#### Scapular stabilization exercise based on the type of SD

In this trial, scapular stabilization exercise is designed based on the manifestation of muscle imbalance for each type of SD. For some muscles, there is a consensus that these muscles need to be strengthened such as the MT<, SA, and RM. Their activation is important for scapular stabilization because these muscles maintain the optimal scapular position during elevation of the arm: upward rotation, external rotation, and posterior tilt [16]. For other muscles such as the PM, LS, UT, and TM, they need to be inhibited. If PM is too tight, it will lead to an increase in scapular anterior tilting and internal rotation and a decrease in scapular upward rotation, resulting in a reduction of the subacromial space [23]. Therefore, it is necessary to strengthen the weak muscles and stretch the tense ones.

All the scapular stabilization exercises in this trial are selected according to the literature regarding scapular muscle dysfunction and new insights derived from recent research [11, 21, 24–30], combined with muscle anatomy and function and clinical experience. Participants in the scapular stabilization exercise group will follow a supervised 6-week exercise program consisting of strengthening exercises (MT<, SA, and RM) and stretching exercises (PM, LS, UT, TM). Appropriate exercises will be given to patients according to the type of SD, and the details of exercises are shown in the Table 2:
Type-1: PM stretching + SA strengthening + MT< strengtheningType-2: TM stretching + SA strengthening + MT< strengthening + RM strengtheningType-3: PM stretching + UT stretching + LS stretching + MT< strengthening

**Table 2 Tab2:** Scapular stabilization exercise

Exercise	Description	Intensity and frequency	Figure
PM stretching	**a.** Subject is standing, the affected arm positioned at wall with elbow flexion into 90°; subject performs stretching with leaning forward. **b.** Subject stands at table and places hands on the edge of the table for support, then performs stretching with squat slowly.	Intensity: It depends on the subjective feeling of the patient—the patient feels slightly tired and slightly shortness of breath (RPE range 11 to 15). Stretching exercise: Each is repeated for 3 times. Strengthening exercise: Each active exercise is progressed from 10 reps*3 sets to 15 reps*3 sets. If subject easily completed 15 reps*3 sets of active exercise, they will go on to resisted exercise. Heavier resistance will be given when the patient can easily complete the lower resistance. Frequency: once a day, for 6 weeks. Time: Stretching exercise: stretch for 5 abdominal breaths at one time, with a 1-min interval between times. Strengthening exercise: the duration of muscle contraction is around 5 seconds, with a 1-min interval between sets.	**a.** **b.**
TM stretching	Subject is standing, slowly performs flexion of the shoulder		
UT stretching	Subject is sitting, with the affected hand pressed under the buttock; subject tips head to the healthy side, and then rotates to the affected side; subject performs stretching with slowly lowering head.		
LS stretching	Subject is sitting, with the affected hand pressed under the buttock; subject tips head to the healthy side, and then rotates to the healthy side; subject performs stretching with slowly lowering head.		
SA strengthening	**Stage 1: active exercise** Subject is standing, with shoulder flexion into 90°; subject slowly performs scapular protraction (A) and retraction (B). **Stage 2: resisted exercise** Subject is standing, holding the elastic band, with shoulder in 90°of forward flexion; subject slowly performs scapular protraction (A) and retraction (B).		**Active exercise** **(A) (B)** **Resisted exercise:** **(A) (B)**
MT< strengthening	**Stage 1: active exercise** Exercise starts with the individual in the side-lying position with the shoulder in neutral position and elbow flexed to 90°(A). Perform external rotation of the shoulder with a towel between the elbow and trunk(B). Avoid compensatory movements. **Stage 2: resisted exercise** The dumbbell as resistance for this exercise, other details are the same as the active exercise.		**Active exercise:** **(A)** **(B)** **Resisted exercise:** **(A)** **(B)**
RM strengthening	**Stage 1: active exercise** Sitting, take a deep breath and extend the shoulders back and pull the elbows back, bringing the scapula as close to the spine as possible, hold for 5 seconds, then slowly return to the starting position while exhaling. **Stage 2: resisted exercise** Subject is sitting, both hands holding the elastic band fixed in front of the body, other details are the same as the above active exercise.		**Active exercise:** **Resisted exercise:**

NOTE. “a” means the more difficult exercise for patients with better shoulder function; “b” means the simpler exercise for patients with poor shoulder function. Choose one of the two exercises according to the patient’s actual ability: teach the patient the exercise “b” if he/she is unable to do the exercise “a.”

Resisted exercises are done with elastic bands (Thera-Band) and dumbbells with different resistance.

Abbreviations: *reps* repetitions, *PM* pectoralis minor, *TM* teres major, *LS* levator scapulae, *UT* upper trapezius, *MT<* middle&lower trapezius, *SA* serratus anterior, *RPE* rating of perceived exertion

#### Traditional rehabilitation training

In the traditional rehabilitation training group, patients will receive the following traditional rehabilitation exercises for periarthritis of the shoulder: pendulum exercise, wall climbing exercise, external rotation exercise (Table 3).

**Table 3 Tab3:** Traditional rehabilitation training

Exercise	Description	Intensity and Frequency	Figure
Wall climbing exercise	Slowly climb up the wall with hands, and then slowly return down to the original position.	Intensity: It depends on the subjective feeling of the patient—the patient feels slightly tired and slightly shortness of breath (RPE range 11 to 15). Each exercise starts with 10 reps*3 sets, and increases 5 reps a week. Frequency: once a day, for 6 weeks. Time: The overall exercise time is 20–30 min.	
Pendulum exercise	The healthy arm is placed on the table to support the body, while the affected arm slowly swings back and forth, side to side, and in circles.		
External rotation exercise	Standing or sitting, hold a stick in hands and bend elbows, then push and pull the stick to both sides with the healthy hand, so as to do internal rotate and external rotate.		

### Outcome assessments

All outcome assessments will be evaluated by well-trained personnel who are blind to the treatment allocation. Assessments will be performed at baseline, 2-, 4-, and 6-week treatment, and at the 6-week follow-up after the end of treatment.

#### Primary outcome measures

Constant-Murley Score (CMS) is a widely used scale in the assessment of shoulder function. The successful application of CMS has proven its validity, reliability, and responsiveness for the detection of shoulder pathologies [31]. The minimal clinically important difference (MCID) considered for the score is 17 points [32]. The CMS includes four aspects related to shoulder pathology: pain, activities of daily living (ADL), range of motion (ROM), and muscle strength. Pain and ADL are answered by the patient; ROM and strength are done by doctors [33]. The score ranges from 0 to 100 points, and higher scores mean better function.

#### Secondary outcome measures

The secondary outcome measures include pain degree, ROM, type of SD, scapula position, and patients’ satisfaction with shoulder joint function. The Lateral Scapular Slide Test (LSST), the Scapular Index (SI), and the Pectoralis Minor Index (PMI) are used to assess scapula position.

Pain intensity at rest, during movement, and sleeping at night are assessed using the numerical rating scale (NRS), with 0 being “No pain,” and 10 being “The worst pain” [34]. The NRS has been shown to be a reliable and valid instrument for the assessment of pain intensity [35, 36]. For the ROM assessment, the electronic goniometer is used to measure active flexion and abduction movements and passive flexion and abduction movements. Previous studies have revealed the electronic goniometer have good validity and reliability [37].

The type of SD is assessed by the comprehensive method combined visual observation and palpation [38]. Subjects are evaluated at rest position in a warm and comfortable environment. Raters make the initial assessment by visual observation, and then put hands on the subject’s bilateral scapula for further identification. This method shows satisfactory inter-reliability [35]. The subjects are assessed by three raters with previous experience with assessments of SD, and raters are allowed discussions to derive a unanimous decision. Subjects whose scapular pattern could not be identified by raters or assessment results are inconsistent among raters will be excluded.

LSST is a quantitative method for assessing inferior angle displacement and recognizing scapular symmetry [39]. The distance from the inferior angle of the scapula to the corresponding thoracic spinous process is measured in three positions: the first position is of the arm relaxed at the sides; the second is hands placed on the lateral iliac crest; and the third is 90° of shoulder abduction and in full internal rotation. A difference of more than 1.5 cm between two sides is considered asymmetric.

SI is calculated by measuring the distance from the sternal notch (SN) to the coracoid process (CP) and the horizontal distance from the posterolateral angle of the acromion (PLA) to the corresponding thoracic spine (TS) with a soft tape measure, using the equation: [(SN to CP/PLA to TS) × 100] [40]. The current study supports SI to measure scapular position because it is correlated with scapular internal rotation [37]. An increase in internal rotation at rest should result in a decreased SN to CP distance and an increased TS to PLA distance, which leads to a smaller SI.

Pectoralis minor length (PML) is divided by the participant’s height and multiplied by 100 to calculate PMI [23]. PMI allows measurements to be normalized to participant’s heights to provide resting PML. This method has been proven to have good validity and reliability [41, 42]. PML is defined as the distance between the coracoid process and the inferior medial aspect of the fourth rib adjacent to the sternocostal junction [23]. The assessment is performed using a flexible tape measure, with the participant standing in a relaxed posture with both arms in a neutral position. To avoid the influence of breathing on the measurement results, it is measured immediately after exhalation. It is reported that pectoralis minor tightness can cause increased scapular anterior tilting, internal rotation, and downward rotation [23, 41, 43].

Patients’ satisfaction with shoulder function is also measured with NRS, with 0 meaning “Extremely unsatisfied with shoulder function,” and 10 meaning “Very satisfied with shoulder function.”

### Follow-up

Follow-up will occur 6 weeks after completion of the treatment program. This time point was selected to assess sustained long-term effectiveness of the intervention.

### Sample size calculation

The study is designed to achieve 95% power overall at the 0.05 significance level to detect change on the CMS between groups after 6 weeks. According to G*Power 3.1 software, we use repeated measurement analysis of variance (ANOVA) (Effect size = 0.25, Number of measurements = 4) to calculate the sample size. Considering a dropout rate of 20%, a sample size of 90 (45 per group) will be needed in this trial.

The statistical hypotheses are:
H0: mean CMS scale (scapular stabilization exercise) = mean CMS scale (traditional rehabilitation training).HA: mean CMS scale (scapular stabilization exercise) ≠ mean CMS scale (traditional rehabilitation training).

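### The stated 95% power does not hold for the stated null hypothesis unless CMS scores at different visits are almost uncorrelated; at an assumed correlation of 0.5 it is about 75%

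*Protocol article*

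**What the plan says.** All of the relevant text is in the Sample size calculation section of the protocol article.

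- Power and target: the study is "designed to achieve 95% power overall at the 0.05 significance level to detect change on the CMS between groups after 6 weeks".
- Method: "According to G*Power 3.1 software, we use repeated measurement analysis of variance (ANOVA"; the inputs given are "Effect size = 0.25, Number of measurements = 4".
- Size: "Considering a dropout rate of 20%, a sample size of 90 (45 per group) will be needed in this trial".
- Hypotheses: "H0: mean CMS scale (scapular stabilization exercise) = mean CMS scale (traditional rehabilitation training", against "HA: mean CMS scale (scapular stabilization exercise) ≠ mean CMS scale (traditional rehabilitation training".

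The section does not say which effect of the ANOVA was powered (between groups, within patients, or group by time). Nor does it give the correlation among the repeated scores, the nonsphericity correction (epsilon), or the number needed before dropout. The Statistical analysis section does not settle the effect, because its list of outcomes for repeated-measures ANOVA does not name the CMS.

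**The concern.** A repeated-measures ANOVA offers several tests, and their sample sizes respond in opposite ways to the correlation among visits. A higher correlation lowers the power of the between-groups test and raises that of the interaction. A power figure therefore means something only for a named effect and an assumed correlation.

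The section does fix the hypothesis: equality of the two group means. That is the between-groups effect, and for it 72 evaluable patients appear too few for 95% power at any ordinary correlation.

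The figure governs how a null result is read. A power of 95% implies a 5% risk of missing the assumed effect. If the risk is nearer 25%, a null result would be taken as a well-powered negative when it is not. The Discussion expects the findings to enter treatment guidelines, so the difference matters.

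**Working it through.** **Inputs from the Sample size calculation section:** f = 0.25, m = 4 measurements, alpha = 0.05, two groups, 20% dropout, 90 patients. Evaluable: 90 × 0.8 = 72, or 36 per arm.

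**Inputs assumed here, because the article does not give them:** correlation among visits (rho) from 0 to 0.9; epsilon = 1 unless stated otherwise.

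**Formulas (noncentral F):**
- Between groups: lambda = f² × N × m / (1 + (m − 1) × rho), with 1 and N − 2 degrees of freedom.
- Group by time: lambda = f² × N × m × epsilon / (1 − rho), with (m − 1) × epsilon and (N − 2) × (m − 1) × epsilon degrees of freedom.

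**Step 1. Attempt to reproduce 90, with rho = 0.5 and epsilon = 1.**
- Between groups: N = 132 gives lambda = 0.0625 × 132 × 4 / 2.5 = 13.2 and power 0.950. After dropout, 132 / 0.8 = 165.
- Group by time: N = 36 gives lambda = 0.0625 × 36 × 4 / 0.5 = 18 and power 0.952. After dropout, 36 / 0.8 = 45 in total.

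Neither gives 90.

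**Step 2. Power of the stated null hypothesis (between groups) with 72 evaluable.** Here f² × N × m = 0.0625 × 72 × 4 = 18.

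| rho (assumed) | lambda = 18 / (1 + 3 × rho) | power |
|---|---|---|
| 0 | 18.0 | 0.987 |
| 0.1 | 13.8 | 0.956 |
| 0.2 | 11.25 | 0.911 |
| 0.3 | 9.47 | 0.859 |
| 0.5 | 7.2 | 0.754 |
| 0.7 | 5.81 | 0.661 |
| 0.9 | 4.86 | 0.585 |

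Power is 0.952 at rho = 0.11 and 0.948 at rho = 0.12, so 95% is reached only at about 0.11 or less. With no dropout at all (N = 90), power at rho = 0.5 is 0.843.

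**Step 3. Routes that do lead to about 90.**
- Group by time, rho = 0, epsilon = 1: N = 71, or 72 for equal arms; 72 / 0.8 = 90.
- Group by time, rho = 0.3, epsilon = 0.6: N = 72; again 90.
- Group by time, rho = 0.4, epsilon = 0.5: N = 71, or 72 for equal arms; again 90.
- Between groups, rho = 0.1: N = 70; 70 / 0.8 = 87.5, so 88.
- Group by time at rho = 0.5, epsilon = 1, with the total of 36 taken as a per-group number: 36 / 0.8 = 45 per group, so 90.

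**Step 4. The effect in CMS points.** With two equal groups, f = 0.25 is a standardised difference of d = 2 × 0.25 = 0.5. The article quotes a minimal clinically important difference of 17 points (Primary outcome measures). The two agree only if the standard deviation is 17 / 0.5 = 34 points. At an assumed standard deviation of 12 to 20 points, d = 0.5 is 6 to 10 points.

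**The case against.** The strongest reply is that the interaction was meant. The power sentence speaks of change between groups after 6 weeks, and four measurements fit baseline to week 6. A difference in change over time is naturally a group-by-time effect. On that reading, 72 evaluable patients give more than 99.9% power at rho = 0.5 and epsilon = 1, and the trial is not short of patients. It is also true that a condensed article may leave the test option, the correlation and epsilon to the full protocol, so their absence alone is not a fault.

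This stands in part. It rules out saying that the trial is underpowered on every reading. It does not rescue the sentence as published, because the hypotheses in the same section compare group means and mention neither change nor interaction. The fault lies in how the published power, inputs, hypotheses and sample size fit together.

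Three stronger readings are tempting, and the documents support none of them.

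- A reader might infer that a total of 36 was mistaken for a per-group number. It fits exactly, but 36 does not appear in the section, and step 3 shows other routes to 90.
- A reader might infer that no reasonable settings lead to 90. That overlooks epsilon: the interaction at moderate correlation with epsilon well below 1 needs about 72.
- A reader might take 75% as the trial's actual power, or carry over the 55% power (about 45% risk of a miss) of an unadjusted week-6 comparison at d = 0.5 with 36 per arm. The first depends on rho = 0.5, which the article never states. The second belongs to a test that the section did not use to size the trial.

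**Conclusion.** The concern holds in a conditional form. For the hypothesis as written, 95% power is not delivered at any ordinary correlation among visits. With 72 evaluable patients the between-groups test has about 91% power at correlation 0.2, falling to 59% at 0.9. At 0.5 it has about 75%, a miss risk of about 25% rather than 5%.

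This rests on f = 0.25, m = 4 and the 20% dropout as stated, on reading the null hypothesis as the between-groups effect, and on the judgement that a correlation of 0.11 or less is low for the same score repeated in the same patients. The origin of the figure of 90 remains open.

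**What to change.** Keep 90 patients and amend the Sample size calculation section as follows.

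1. Name the effect that tests the null hypothesis on the CMS, the assumed correlation among visits, epsilon if the effect involves time, and the number needed before dropout.
2. Replace the 95% figure with the power that 36 evaluable patients per arm give for that test over a plausible range of correlations. For the between-groups test this is about 75% if 0.5 is assumed, and 86% to 66% over 0.3 to 0.7.
3. Express the detectable difference in CMS points, with the assumed standard deviation, so that it can be set beside the 17-point threshold.
4. If the interaction is the intended test, restate the hypotheses to match and report its power with the correlation and epsilon used.

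The cost is a wording amendment, with no extra patients. The drawback is that the stated power for the current null hypothesis becomes less favourable.

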### Randomization and allocation concealment

Consented eligible participants will be randomly allocated to one of the two groups in a ratio of 1:1. Patients’ allocations will be according to a computer-generated randomization table. Generation of the allocation sequence, enrollment of participants, and assignment of participants to interventions will be done by the main researcher of the trial. When the subject is enrolled into the study, the subject will be assigned a study number sequentially. If the subject drops out of the study, the assigned study number will not be reused. The block size will not be known until the end of the study for allocation concealment. The random numbers will be sealed in envelopes by an individual other than the trial researchers. The envelopes will be randomly selected by the patients, and they would be assigned to the intervention or control groups according to the contents of the envelope.

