### Blinding

The therapist and patients will not be blinded because of the nature of the intervention, but it is feasible to make the researchers, outcome evaluators, and statisticians blinded to the group/treatment assignment. Furthermore, the outcome evaluation will be done by well-trained personnel in order to minimize bias. After the completion of data analysis, the statistician will present un-blinded data to the researchers.

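### Allocation concealment is not secured: one researcher generates the sequence, enrols and assigns, and the text conflicts on whether the table or the patient's draw decides treatment

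*Protocol article*

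**What the plan says.** All statements below come from the protocol article; unless another section is named, they stand under Randomization and allocation concealment.

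- Ratio and source: "Consented eligible participants will be randomly allocated to one of the two groups in a ratio of 1:1", and "allocations will be according to a computer-generated randomization table".
- Roles: "Generation of the allocation sequence, enrollment of participants, and assignment of participants to interventions will be done by the main researcher of the trial".
- Numbering: "When the subject is enrolled into the study, the subject will be assigned a study number sequentially".
- Blocks: "The block size will not be known until the end of the study for allocation concealment". No size is given, and no exception is made for the person who generates the list.
- Envelopes: "The random numbers will be sealed in envelopes by an individual other than the trial researchers". Then: "The envelopes will be randomly selected by the patients", with the contents deciding the group.
- Blinding section: "it is feasible to make the researchers, outcome evaluators, and statisticians blinded to the group/treatment assignment". The same section has the statistician show unblinded data to the researchers only once the analysis is complete.

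The Study design section names five hospitals. Neither it nor the randomization section mentions stratification by hospital. The Trial status section says the trial is underway.

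**The concern.** Concealment works by keeping the person who decides whether a patient enters from knowing what that patient would receive. Here one researcher produces the sequence, decides on enrolment and makes the assignment. Such a person would ordinarily know the blocks, and having assigned patients cannot be blinded to their assignment.

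Some eligibility decisions need judgement. Examples in the Exclusion criteria are whether body-surface landmarks are clear enough for assessment and whether another disease makes a patient unfit for the programme. A recruiter who can foresee the next allocation could, even without intent, apply these criteria differently for the two arms. Blinded outcome assessment does not correct that, because the groups would already differ at entry.

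A second problem is that the section gives two mechanisms for deciding treatment, and they are not the same mechanism.

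**Working it through.** The plan states no figure on this point, so there is nothing to reproduce. The check is a comparison of statements, followed by illustrations on stated assumptions.

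**1. Roles against the other statements.**
- Main researcher generates the sequence; block size unknown until the end. These agree only if the generator is kept from the block size, and no means of doing so is described.
- Main researcher assigns participants; researchers are blinded to assignment. These cannot both hold for the main researcher.
- An outside person seals the envelopes. This protects the envelope contents from view at the bedside. It does not change who produced the sequence inside them.

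**2. What decides treatment: two readings.**
- *Envelopes follow the table.* Study number k receives list entry k. Whoever generated the list may know entry k before enrolling patient k.
- *Patients draw freely from the sealed envelopes.* Knowing the list no longer reveals the next envelope. But study number k is no longer tied to list position k, and the blocks do nothing.

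Each reading removes one problem and leaves the other. The text does not choose between them.

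**3. First reading: how much could be foreseen.** Assume permuted blocks of size 2m in a 1:1 ratio, and a recruiter who knows m and all past allocations but not the list. An allocation is certain once one arm of the block is used up. The expected number of such allocations per block is 2m/(m+1), so their share is [2m/(m+1)]/(2m) = 1/(m+1).

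| Block size (assumed) | Share certain | Best-guess accuracy (simulated) |
|---|---|---|
| 2 | 1/2 = 50% | 75% |
| 4 | 1/3 = 33% | 71% |
| 6 | 1/4 = 25% | 68% |
| 8 | 1/5 = 20% | 67% |

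Without foresight, best-guess accuracy is 50%. A recruiter who still had the list itself would know every allocation, but the document does not say who keeps it.

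**4. Second reading: what the draw does to the blocking.** Assume one pool of 90 envelopes, 45 per arm (total from the Sample size calculation section). After 60 draws the count in one arm is hypergeometric (90, 45, 60). The SD of the between-arm difference is 2 × √(60 × 0.25 × 30/89) = 4.5, and the chance of a difference of 6 or more is 26%. Blocks of 4 used in order never allow a difference above 2.

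The cost in precision is small. At 33:27 the efficiency relative to an equal split is 4 × 33 × 27/60² = 3564/3600 = 0.99. If the whole pool is used, the final split is 45:45.

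**5. Does the draw harm balance within hospitals?** Assume 90/5 = 18 patients per hospital.
- Free draw from one 45/45 pool: chance of 12:6 or worse at a given hospital = 0.187.
- One unstratified blocked list used strictly in order, with hospitals' patients arriving interleaved at random (simulated): 0.187, 0.186, 0.186 and 0.186 for blocks of 2, 4, 6 and 10.
- At least one such hospital among five: about 59% either way. Treating hospitals as independent gives 1 − (1 − 0.187)^5 = 64%, which is too high because they share one pool.

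The draw makes no difference to hospital balance unless the list was to be stratified by hospital, and the article does not say that it was.

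**The case against.** The strongest reply is that the plan does contain safeguards. Someone outside the research team seals the envelopes, the block size is to be withheld, and a genuine blind draw from sealed envelopes is hard to foresee even for the person who made the list. This stands in part. It is why the conclusion is that concealment is not secured, and not that allocation is open. It does not settle the matter, because the plan relies on the table as well as the draw, and the role statement gives all three tasks to one person.

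A second reply is that the Blinding section says only that blinding of researchers is feasible, and that the Study design section commits only to blinded evaluators and data collectors. That softens the conflict. But the Blinding section also withholds unblinded data from the researchers until the analysis is done, which cannot apply to someone who made the assignments.

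A third reply is that an article leaves detail to the full protocol. This covers envelope opacity, numbering and logs. It does not cover statements that the article makes and that contradict each other.

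Four stronger readings may tempt a reader, and the document does not support them:
- *Balance within the five hospitals is lost through the draw.* No stratification is stated, and step 5 shows the same imbalance with an unstratified list used in order.
- *Allocation cannot be audited.* Study numbers are sequential and not reused, and a log linking envelopes to the table may exist in the full protocol.
- *Selection bias is without limit because the recruiter holds the list.* The text says who generates the sequence, not who keeps it.
- *Patient-reported pain and daily activities in the Constant-Murley score make the selection bias worse.* Those items are open to bias because patients are unblinded, which the plan acknowledges and which is a separate matter.

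**Conclusion.** The concern holds as a defect in stated procedure. Role separation is absent, the block-size and blinding statements conflict with the role statement, and the section gives two incompatible rules for what determines treatment. Independent sealing lessens the risk but does not remove it.

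The size of any resulting bias cannot be derived from the document. The 20% to 50% of allocations that could be foreseen with certainty rests on assumed permuted blocks of 8 down to 2, envelopes used in list order, and a recruiter who knows the block size and past allocations. Under a true free draw that risk is much weaker. What is then lost is the function of the blocked table, at little cost in precision.

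The point still needs correction: every comparison in the trial rests on the allocation, and a later analysis cannot undo selection at entry.

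**What to change.** 1. Have the outside person who already seals the envelopes also generate and hold the allocation list, including the block size.
2. Use sequentially numbered opaque envelopes, opened strictly in order, and only after consent, eligibility and baseline assessment are recorded.
3. Delete the step in which patients pick an envelope.
4. Limit the main researcher to enrolment, and reword the Blinding section to name which researchers are blinded.
5. As the trial is underway, state what has actually been done and report how many patients were allocated under the procedure now described.

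A separate envelope series per hospital is an optional addition; it is the step that would give balance within hospitals.

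The cost is a short procedural amendment. The independent person is already in the plan, so no staff are added, and the sample size and analysis are unaffected.
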